**Summary of Changes in the Condi 2 protocol Version 4; May 27, 2013 original approved in 2013 to the current applicable Version 10.6 January 2017**

- The study period started in 2013 and was to complete in 2016 but got prolonged with termination in 2019
- The number of patients to include was extended from 2300 – first to 4300 then to 5700. Due to a lower than expected event rate

**First:**

To detect a 25% reduction in CV mortality in the RIC-treated group (from 17.4% to 13.0%), with a power of 80% and a significance level of 5%, a sample size of 1044 patients will be required for each trial arm (2088 in total). To account for and failure of fulfilling entry criteria on arrival we plan to include 2300 patients.

**Second**

In 2015: To demonstrate a 25% reduction in the primary composite endpoint in the RIC-treated group (from 11.0% to 8.25%), with 80% power and at the 5% significance level, would require 1,805 patients per treatment arm which equates to 3,610 patients in total. Therefore, we will need to recruit 4,300 all-comer STEMI patients

**Finally**

In 2016: To detect a 25% reduction in cardiac mortality in the RIC-treated group (from 8% to 6%), with a power of 80% and a significance level of 5%, a sample size of 2,553 patients will be required for each trial arm ( 5106 in total). To account for and failure of fulfilling entry criteria on arrival we plan to include 5,700 patients.

- The primary endpoint was detailed as
  - Cardiovascular mortality and hospitalisation for heart failure at one year.But was in 2015 specified as
  - Cardiac mortality and hospitalisation for heart failure at one year
- The follow up echo was scheduled for 3 months but the period was expanded to include the period between 3 to 6 months

[figure not shown]

Effect of Remote  
Ischaemic Conditioning  
on clinical outcomes in ST-  
elevation myocardial  
infarction patients  
undergoing Primary  
Percutaneous Coronary  
Intervention

[figure not shown]

Effect of Remote Ischaemic Conditioning  
on clinical outcomes in ST segment elevation  
myocardial infarction patients undergoing  
Primary Percutaneous Coronary Intervention

## • INTRODUCTION

This Statistical Analysis Plan (SAP) describes the planned analysis for the CONDI-2 and ERIC-PPCI trials titled: Effect of Remote Ischaemic Conditioning on clinical outcomes in ST-segment elevation myocardial infarction patients undergoing Primary Percutaneous Coronary Intervention. Procedures for combining and reporting the relevant data from the two trials are not covered in this document. However, the specific data to be shared and made available to both study groups will be discussed and agreed between the CONDI-2 and ERIC-PPCI trial teams. It is expected that the relevant, cleaned data from each trial will be supplied as Excel spreadsheets.

Detailed descriptions of each trial can be found in the respective protocols and SAPs for each trial. This document should be read in conjunction with the Research Agreement between CONDI-2 and ERIC-PPCI version 3.0, dated 25th January 2016 together with the 1st Amendment dated 6th March 2017. In brief, the intention and purpose of the collaboration is that main trial outcomes and anonymised patient level data from each study will be merged and analysed although the primary publication will also provide results broken down by trial.

This SAP describes the data and analyses for the primary publication and not for the sub-study data. The trial statisticians from CONDI-2 and ERIC-PPCI will undertake the analyses, and discuss and resolve any discrepancies with the wider trial groups if necessary to ensure the integrity and accuracy of the results. In order for the data to be analysed as accurately and efficiently as possible a preliminary transfer of the agreed data (excluding the randomised treatment) before the trial end will occur. The timelines for the transfer of the preliminary and final data will be discussed and agreed between the trial teams.

## • STUDY OBJECTIVES AND SAMPLE SIZE

The objectives for the combined analysis are as follows:

### ○ Primary Objective

To determine the effect of Remote ischaemic conditioning (RIC) on the combined endpoint of cardiac death and/or hospitalisation for heart failure (HHF) at 12

months in STEMI patients undergoing primary percutaneous coronary intervention (PPCI).

### ○ Secondary Objectives

To determine the effects of RIC on:

- Rates of the individual components of the primary endpoint at 12 months
- Rates of the combined endpoint as well the individual components of cardiac death and/or HHF at 30 days.
- Rates of the individual endpoints of all-cause death, repeat coronary revascularisation, reinfarction, stroke at 30 days and 12 months.

### ○ Sample Size

The primary combined endpoint will be cardiac death and HHF at 12 months. As a conservative estimate a combined cardiac death and HHF event rate of 8.5% at 12 months in the conservative arm for all-comer STEMI patients will be used. To demonstrate a 25% reduction in the primary composite endpoint in the RIC-treated group (from 8.5% to 6.4%), with 80% power and at the 5% significance level, 2395 patients per treatment arm are required which equates to 4790 patients in total. Therefore, 5400 STEMI patients will be recruited (allowing for a 10% drop out rate at 12 months) between Denmark and the UK (2600 STEMI patients in Denmark and 2800 STEMI patients in the UK). If the event rate in the control arm is higher than the estimated 8.5% or the losses less than 10% then the power will increase.

## ● DATA PROVISION

Detail of the variables to be combined and analysed will be provided in the parallel document detailing the logistics and timeframe for combining and analysing the data from CONDI-2 and ERIC-PPCI.

## ● ANALYSIS POPULATIONS

### ○ Definition of Populations for Analysis

The primary analysis will be performed on an intention to treat basis, by including all patients where possible according to the group to which they were randomised irrespective of whether they received the intervention as allocated.

A secondary per protocol analysis will be undertaken including only patients who receive the allocated intervention as intended.

- **Intent-to-treat (ITT)**

The intent-to-treat analysis population will include all patients randomised to CONDI-2 and ERIC-PPCI regardless of whether they received their randomised intervention as specified (i.e. including all patients whether or not all cycles of RIC or sham RIC were fully completed according to protocol and whether or not the patient received PPCI).

- **Per Protocol (PP)**

The per protocol analysis population will include confirmed STEMI patients randomised to CONDI-2 and ERIC-PPCI who received their randomised intervention as specified (i.e. including patients where all four cycles of RIC or sham RIC were fully completed according to protocol and the patient received PPCI).

- **STATISTICAL ANALYSIS**

- **General**

The final combined statistical analysis will be performed as pre-specified in this SAP. Any, additional, post-hoc, exploratory analyses completed to support these planned analyses which are presented in the trial reports but not included in this SAP, will be clearly identified as such. Analyses will adjust for trial (i.e. CONDI-2 or ERIC-PPCI) where indicated below.

- **Methods for Handling Missing Data**

For the outcomes considered in this analysis, missing data are expected to be minimal. However, multiple imputation methods may be used depending on the scale and pattern of the missing data.

- **Analysis of Primary Endpoint – cardiac death and hospitalisation for heart failure 12 months after randomisation.**

The primary combined endpoint is defined as the first occurrence of HHF or cardiac death within 12 months of randomisation. The primary analysis will be a

comparison of the rate of the first occurrence of cardiac death or HHF between the RIC and control arms of the trial. Hazard ratios and 95% confidence intervals will be calculated using Cox proportional hazards modelling, stratified by trial, and Kaplan-Meier curves will be produced. The time scale used for survival analysis will be time to the primary endpoint since randomisation. Participants will be censored if they die of a non-cardiac cause, are lost to follow-up, withdraw from the study, or at 12 months after randomisation. The assumptions underlying the Cox model will be assessed and if there is clear non-proportionality hazard ratios will be presented separately for the relevant time periods.

In addition risk differences at one year, again stratified by trial, will also be calculated together with 95% confidence intervals.

- Analysis of Secondary, and Other Efficacy Endpoints

- Cardiac death and HHF at 30 days

The RIC and control arms of the trial year will be compared on rate of the first occurrence of cardiac death or HHF up to 30 days following randomisation. Hazard ratios and 95% confidence intervals will be calculated using Cox proportional hazards modelling, stratified by trial, and Kaplan-Meier curves will be produced. The time scale for analysis will be time since randomisation. Participants will be censored if they die, are lost to follow-up, withdraw from the study, or at 30 days after randomisation. The risk difference stratified by trial together with 95% confidence intervals will also be calculated.

- Individual components of cardiac death and HHF at 30 days and 12 months

Survival analysis will be used to examine the individual components of the composite outcome, using the same methods as outlined above.

- All cause death, repeat coronary revascularisation, re-infarction, stroke at 30 days and 12 months

Survival analysis will be used to examine each of these clinical outcomes, using the same methods as outlined above.

### Repeat HHF and cardiac death

In order to take account of recurrent HHFs in patients while also accounting for the competing mortality, a parametric joint frailty model will be used for outcomes up to 12 months adjusted for trial. The aim is to analyse repeat HHFs while accounting for their associated mortality risk by specifying distributions for recurrent HHFs and for time to cardiac mortality, and including individual-specific latent variables to allow for an association between the two event processes. This results in a hazard ratio and 95% CI for recurrent HHF which takes into account mortality as informative censoring as well as a hazard ratio and 95% CI for cardiac death. If there are any problems encountered with model development a negative binomial model will be used.(1-3)

#### ○ Subgroup analysis

A limited number of pre-specified subgroup analyses are planned on the primary outcome. These will be limited to age, diabetic status, LAD vs non-LAD STEMI, TIMI flow (0-1 and 2-3) pre-angioplasty and time of first medical contact to PPCI (i.e. balloon time). The subgroups will be analysed by inclusion of an interaction term between treatment group and the subgroup in the Cox regression model.

## Appendix: Figures

Figure 1: Trial flow diagram ERIC-PPCI

[figure not shown]

Figure 2: Trial flow diagram CONDI 2

[figure not shown]

[figure not shown]

Effect of Remote  
Ischaemic Conditioning  
on clinical outcomes in ST-  
elevation myocardial  
infarction patients  
undergoing Primary  
Percutaneous Coronary  
Intervention

[figure not shown]

Effect of Remote Ischaemic Conditioning  
on clinical outcomes in ST segment elevation  
myocardial infarction patients undergoing  
Primary Percutaneous Coronary Intervention

## • INTRODUCTION

This Statistical Analysis Plan (SAP) describes the planned analysis for the CONDI-2 and ERIC-PPCI trials titled: Effect of Remote Ischaemic Conditioning on clinical outcomes in ST-segment elevation myocardial infarction patients undergoing Primary Percutaneous Coronary Intervention. Procedures for combining and reporting the relevant data from the two trials are not covered in this document. However, the specific data to be shared and made available to both study groups will be discussed and agreed between the CONDI-2 and ERIC-PPCI trial teams. It is expected that the relevant, cleaned data from each trial will be supplied as Stata data files (version 13).

Detailed descriptions of each trial can be found in the respective protocols and SAPs for each trial. This document should be read in conjunction with the Research Agreement between CONDI-2 and ERIC-PPCI version 3.0, dated 25th January 2016 together with the 1st Amendment dated 6th March 2017. In brief, the intention and purpose of the collaboration is that main trial outcomes and anonymised patient level data from each study will be merged and analysed although the primary publication will also provide results broken down by trial.

The trial statisticians from CONDI-2 and ERIC-PPCI will undertake the analyses, and discuss and resolve any discrepancies with the wider trial groups if necessary to ensure the integrity and accuracy of the results. In order for the data to be analysed as accurately and efficiently as possible a preliminary transfer of the agreed data (excluding the randomised treatment) before the trial end will occur. The timelines for the transfer of the preliminary and final data will be discussed and agreed between the trial teams.

## • STUDY OBJECTIVES AND SAMPLE SIZE

The objectives for the combined analysis are as follows:

### ○ Primary Objective

To determine the effect of Remote ischaemic conditioning (RIC) on the combined endpoint of cardiac death and/or hospitalisation for heart failure (HHF) at 12 months in STEMI patients undergoing primary percutaneous coronary intervention (PPCI).

## ○ Secondary Objectives

To determine the effects of RIC on:

- Rates of the individual components of the primary endpoint at 12 months
- Rates of the combined endpoint as well the individual components of cardiac death and/or HHF at 30 days.
- Rates of the individual endpoints of all-cause death, repeat coronary revascularisation, reinfarction, stroke at 30 days and 12 months.

## ○ Sample Size

The primary combined endpoint will be cardiac death and HHF at 12 months. As a conservative estimate a combined cardiac death and HHF event rate of 8.5% at 12 months in the conservative arm for all-comer STEMI patients will be used. To demonstrate a 25% reduction in the primary composite endpoint in the RIC-treated group (from 8.5% to 6.4%), with 80% power and at the 5% significance level, 2395 patients per treatment arm are required which equates to 4790 patients in total. Therefore, 5400 STEMI patients will be recruited (allowing for a 10% drop out rate at 12 months) between Denmark and the UK (2600 STEMI patients in Denmark and 2800 STEMI patients in the UK). If the event rate in the control arm is higher than the estimated 8.5% or the losses less than 10% then the power will increase.

## ● DATA PROVISION

Detail of the variables to be combined and analysed will be provided in the parallel document detailing the logistics and timeframe for combining and analysing the data from CONDI-2 and ERIC-PPCI.

## ● ANALYSIS POPULATIONS

### ○ Definition of Populations for Analysis

The primary analysis will be performed on an intention to treat basis, by including all patients where possible according to the group to which they were randomised irrespective of whether they received the intervention as allocated. A secondary per protocol analysis will be undertaken including only patients who receive the allocated intervention as intended.

- Intent-to-treat (ITT)

The intent-to-treat analysis population will include all patients randomised to CONDI-2 and ERIC-PPCI regardless of whether they received their randomised intervention as specified (i.e. including all patients whether or not all cycles of RIC or sham RIC were fully completed according to protocol and whether or not the patient received PPCI).

- Per Protocol (PP)

The per protocol analysis population will include confirmed STEMI patients randomised to CONDI-2 and ERIC-PPCI who received their randomised intervention as specified (i.e. including patients where all four cycles of RIC or sham RIC were fully completed according to protocol and the patient received PPCI).

- STATISTICAL ANALYSIS

- General

The final combined statistical analysis will be performed as pre-specified in this SAP. Any, additional, post-hoc, exploratory analyses completed to support these planned analyses which are presented in the trial reports but not included in this SAP, will be clearly identified as such. Analyses will be stratified by trial (i.e. CONDI-2 or ERIC-PPCI) where indicated below.

- Methods for Handling Missing Data

For the outcomes considered in this analysis, missing data are expected to be minimal. However, multiple imputation methods may be used depending on the scale and pattern of the missing data.

- Analysis of Primary Endpoint – cardiac death and hospitalisation for heart failure 12 months after randomisation.

The primary combined endpoint is defined as the first occurrence of HHF or cardiac death within 12 months of randomisation. The primary analysis will be a comparison of the rate of the first occurrence of cardiac death or HHF between the RIC and control arms of the trial. Hazard ratios and 95% confidence intervals will be calculated using Cox proportional hazards modelling, stratified by trial,

and Kaplan-Meier curves will be produced. The time scale used for survival analysis will be time to the primary endpoint since randomisation. Participants will be censored if they die of a non-cardiac cause, are lost to follow-up, withdraw from the study, or at 12 months after randomisation. The assumptions underlying the Cox model will be assessed and if there is clear non-proportionality hazard ratios will be presented separately for the relevant time periods.

In addition risk differences at one year, again stratified by trial, will also be calculated together with 95% confidence intervals.

- **Analysis of Secondary, and Other Efficacy Endpoints**

- Cardiac death and HHF at 30 days**

The RIC and control arms of the trial year will be compared on rate of the first occurrence of cardiac death or HHF up to 30 days following randomisation. Hazard ratios and 95% confidence intervals will be calculated using Cox proportional hazards modelling, stratified by trial, and Kaplan-Meier curves will be produced. The time scale for analysis will be time since randomisation. Participants will be censored if they die, are lost to follow-up, withdraw from the study, or at 30 days after randomisation. The risk difference stratified by trial together with 95% confidence intervals will also be calculated.

- Individual components of cardiac death and HHF at 30 days and 12 months**

Survival analysis will be used to examine the individual components of the composite outcome, using the same methods as outlined above.

- All cause death, repeat coronary revascularisation, reinfarction, stroke at 30 days and 12 months**

Survival analysis will be used to examine each of these clinical outcomes and MACCE (all-cause death, repeat coronary revascularisation, reinfarction, or stroke) using the same methods as outlined above.

- Repeat HHF and cardiac death**

In order to take account of recurrent HHF in patients while also accounting for the competing mortality, a parametric joint frailty model will be used for

outcomes up to 12 months adjusted for trial. The aim is to analyse repeat HHFs while accounting for their associated mortality risk by specifying distributions for recurrent HHFs and for time to cardiac mortality, and including individual-specific latent variables to allow for an association between the two event processes. This results in a hazard ratio and 95% CI for recurrent HHF which takes into account mortality as informative censoring as well as a hazard ratio and 95% CI for cardiac death. If there are any problems encountered with model development a negative binomial model will be used.(1-3) Repeat HHFs alone will be analysed using a negative binomial model.

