### 35.2. Sham RIC

An autoRIC™ cuff visually identical to that used in the RIC protocol, or manual cuff, will be placed on the upper arm and a simulated RIC protocol applied. Inflation will be simulated and held for 5 minutes, deflation will then be simulated and held for five minutes, a cycle which will be undertaken 4 times in total.

The sham device's components and external appearance are identical to that of the autoRIC™. However, as compared to the autoRIC™, the sham device control unit's pump is disconnected such that the control unit cannot inflate the applicator cuff. The sham device provides the same sound and vibration as that of the pump inflating and the same LED indicators on the control unit. The operation of the autoRIC™ control unit with respect to the (simulated) RIC procedure initiation, cycle indication, and termination are identical in the sham device, with the exception that the applicator cuff does not inflate.

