### 35.4. Duration of treatment

Although the RIC / sham RIC protocol lasts 40 minutes in total, the cuff should be removed after the 4th cycle of inflation and the last 5 min of reperfusion undertaken with the cuff removed. This means that after 35 min the intervention is completed. In the cases where the door to PPCI time is less than 35 min, the RIC / sham RIC protocol may overlap with the beginning of the PPCI procedure when the coronary angiogram is being performed.

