The admitting ambulance doctor, the doctor at the receiving hospital, or the paramedic will orally inform the patient based on the short written information (B) and hand out the written informations (A+B). After oral and written informed consents are obtained the patient will sign the agreement form and be randomised via a secure web site to pPCI with or without RIC by the doctor on duty at one of the receiving hospitals. Computer-generated blocked randomisation lists, stratified by centre, will be prepared in advance of the study.

After information is given in the acute phase, the patient does not have much time for reflection before signing the informed consent form. Therefore, a study nurse will give the patient additional oral information after the acute phase by or the doctor performing the pPCI based on the full written information (A). Both during the first and second stage of information it will be emphasised that the patient has the right to withdraw his/her informed consent at any time.

- **Procedures and treatment**

*Control group:* Will be treated according to standard procedures in the ambulance.

*Intervention group, RIC group:* The CellAegis auto RIC (automated blood pressure cuff) will be placed on the upper arm and inflated to 200mmHg for 5 minutes and then deflated for 5 minutes, a programmed cycle which is repeated 4 times in total (therefore the total length of the RIC protocol is 40 minutes). If the initial systolic blood pressure is >175mmHg, a manual cuff will be used to and inflated to 25mmHg above the systolic blood pressure. In recruiting centres where randomisation occurs at the hospital or in cases with short transportation time, the RIC protocol will continue during PCI until successful or until immediately before reperfusion.

Further, the patients will be treated according to standard procedures in the ambulance.

|                                                    | Acute intervention |         | Index event    | Follow up |
|----------------------------------------------------|--------------------|---------|----------------|-----------|
| Randomisation                                      | Intervention       | Control |                |           |
| Blood samples                          |                    |         | X              |           |
| e-CRF                                  |                    |         | X              | X         |

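### In the secondary per-protocol analysis only, the four-cycle test in SAP v3 section 4.3 does not fit CONDI-2: it removes either every control or, one-sidedly, RIC patients stopped before reperfusion as that protocol directs

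*Supplement*

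**What the plan says.** SAP v3 section 4.1 makes intention to treat the primary analysis and adds: "A secondary per protocol analysis will be undertaken including only patients who receive the allocated intervention as intended". Section 4.3 limits the per-protocol set to patients with confirmed STEMI who received their allocated intervention as specified. It explains this for both trials together as "including patients where all four cycles of RIC or sham RIC were fully completed according to protocol and the patient received PPCI". Section 4.2 keeps all randomised patients in the intention-to-treat set whatever their cycle count.

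CONDI-2 v10, Procedures and treatment, describes an automated course of four cycles lasting 40 minutes, then qualifies it. "In recruiting centres where randomisation occurs at the hospital or in cases with short transportation time", it says, "the RIC protocol will continue during PCI until successful or until immediately before reperfusion". The control group receives no cuff procedure: "Will be treated according to standard procedures in the ambulance".

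ERIC-PPCI v5 differs on both counts. Its control arm has a sham course (section 35.2): "deflation will then be simulated and held for five minutes, a cycle which will be undertaken 4 times in total". Section 35.4 says that when door-to-PPCI time is short, "the RIC / sham RIC protocol may overlap with the beginning of the PPCI procedure when the coronary angiogram is being performed"; it sets no stop at reperfusion.

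**The concern.** A per-protocol set should hold the patients treated as their own protocol directed. In CONDI-2 the four-cycle test does something else. A RIC patient randomised at the hospital and reperfused before the fourth cycle ends has been treated correctly but fails the test. A control with the same short time has no cycles to count.

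If controls are kept, RIC patients are removed according to time from cuff start to reperfusion and controls are not. The CONDI-2 part of the analysis then compares a selected RIC arm with an unselected control arm. If prognosis varies with that time, a difference can appear with no treatment effect. At stake is the reading of one prespecified secondary analysis.

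**Working it through.** **1. Apply the section 4.3 test to each arm.**

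| Arm | Procedure in its protocol | Result of the four-cycle test |
|---|---|---|
| ERIC-PPCI RIC | four cycles, overlap with PPCI allowed | can be passed or failed |
| ERIC-PPCI sham | four simulated cycles | same test as the RIC arm |
| CONDI-2 RIC | four cycles, or stopped just before reperfusion in the stated settings | a protocol-directed stop fails |
| CONDI-2 control | standard care, no sham | read literally, all fail; on the workable reading, all stay, subject to confirmed STEMI and PPCI |

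The mismatch is therefore confined to CONDI-2.

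**2. Who can be affected.** One cycle is 5 + 5 = 10 minutes, so four take 40. The fourth inflation ends at 3 × 10 + 5 = 35 minutes. Only CONDI-2 RIC patients under the stop rule and reperfused less than 35 to 40 minutes after cuff start can be excluded this way.

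**3. The plan's own figure.** The point rests on no stated number. The nearest is the sample size in SAP v3 section 2.3. With 8.5% against 6.375% (a 25% reduction), two-sided 5%, 80% power and no continuity correction, I get 2393 per arm against the stated 2395. That figure is sound and is not touched by this point.

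**4. Illustrative size.** From section 2.3: 2600 CONDI-2 patients, 2800 ERIC-PPCI patients, 8.5% control risk. Assumed, because the documents do not say:
- 1:1 allocation, so 1300 and 1400 per arm;
- a share f = 0.8 to 1.0 with confirmed STEMI and PPCI, equal in all arms;
- a share s of these who would be stopped under the rule;
- a risk ratio k for them against the rest;
- no true effect, and 8.5% risk in every arm before exclusion.

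RIC patients excluded = 1300 × f × s; controls excluded on this ground = 0.

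Spurious CONDI-2 risk ratio = 1 / (s·k + 1 − s). For s = 0.25 and k = 0.7 this is 1 / (0.175 + 0.75) = 1.081.

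Pooling is by inverse variance of the log risk ratio, with ERIC-PPCI at 1.0.

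| s | RIC excluded (f = 0.8 to 1.0) | CONDI-2 ratio, k = 0.7 / 1.3 | Pooled ratio, k = 0.7 / 1.3 |
|---|---|---|---|
| 0.05 | 52 to 65 | 1.015 / 0.985 | 1.007 / 0.993 |
| 0.10 | 104 to 130 | 1.031 / 0.971 | 1.014 / 0.986 |
| 0.25 | 260 to 325 | 1.081 / 0.930 | 1.036 / 0.969 |

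At k = 1 every ratio is 1.000. The pooled standard error of the log risk ratio at f = 1.0 is 0.090 to 0.094, so the shift at s = 0.25 is 0.39 (k = 0.7) or 0.33 (k = 1.3) standard errors. As a stress case, k = 0.5 or 2.0 at s = 0.25 gives pooled ratios of 1.064 or 0.913, which is 0.68 or 0.95 standard errors. The table illustrates the bias and does not bound it.

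**The case against.** The strongest reply is that the SAP wording is partly open. Section 4.1 speaks of the intervention being received as intended, and 4.3 of completion according to protocol. If those phrases govern, a stop that CONDI-2 directs is compliant and the asymmetry largely disappears. It is also fair that keeping controls relies on the general phrase while excluding RIC patients relies on the explanation that follows it. This stands in part: an analyst could build the set either way. But the explanation asks for all four cycles, fully completed, and that is the only operational rule given. Taken as written, it either drops all CONDI-2 controls or removes compliant RIC patients.

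Second, the separate trial SAPs (SAP v3 Introduction) and the parallel document on variables (Data Provision) are not shown and may settle the matter. They may, but the combined SAP gives its own definition and says that the final analysis will follow it.

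Third, a uniform four-cycle set is a legitimate full-dose population. Agreed; it is a different population from patients treated as specified and should be labelled so.

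Fourth, the affected group may be small. CONDI-2 v10 prefers randomisation in the ambulance or on arrival, and the stop clause covers only some patients. This stands. The shares used above have no anchor in the documents.

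A reader might infer more: that the plan really intends to discard the CONDI-2 controls, that the per-protocol result is biased in a known direction, or that ERIC-PPCI or the primary result is compromised. The documents support none of these. Discarding all controls would leave no CONDI-2 comparison. Neither the share stopped nor their prognosis is given. ERIC-PPCI tests both arms alike, and intention to treat ignores cycle counts.

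**Conclusion.** The point holds as a minor one, limited to the CONDI-2 part of the secondary per-protocol analysis. Section 4.3 has no workable rule for CONDI-2 controls. On the reading that keeps them, it can exclude RIC patients whose course ended as CONDI-2 v10 directs, with no matching exclusion of controls.

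The size and direction of any bias cannot be told from the documents. For 5% to 25% stopped and a risk ratio of 0.7 to 1.3, the pooled shift is at most about 4% and under 0.4 of a standard error; more extreme prognostic differences would enlarge it, and equal risk would remove it. These shares, the risk ratios, 1:1 allocation and the absence of a true effect are assumptions. The primary analysis, significance level and sample size do not change.

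**What to change.** Amend SAP section 4.3 for CONDI-2 as follows:

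- **Controls** are per protocol if they had confirmed STEMI, received PPCI and received no RIC.
- **RIC patients** are per protocol if they had confirmed STEMI, received PPCI, and RIC was started and either completed four cycles or was stopped immediately before reperfusion under the CONDI-2 rule. Set no minimum cycle count: a minimum has no basis in the protocol and would again exclude the fastest RIC patients but not equally fast controls.
- **Four-cycle definition:** report it alongside as a full-dose sensitivity analysis, with cycles completed tabulated by trial and arm.
- **If protocol-directed stops cannot be identified** from the recorded data, say so and label the CONDI-2 four-cycle result as selected on the RIC arm only.

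ERIC-PPCI keeps its present test. The cost is SAP wording, one extra run and one table. Cycle counts are already needed by the current definition. The documents do not show whether CONDI-2 records a stop reason or cuff times, although its planned subgroup on time from end of RIC to pPCI suggests that some timing data are collected.

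The downside is that dose then differs between the trials in the per-protocol set; the four-cycle sensitivity analysis shows what that changes. Exclusions for device failure or intolerance in CONDI-2 still fall on the RIC arm only, so the per-protocol result should be presented as supportive.
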